### Data collection and management

The nominated division within state health departments (CEC, CEQ and SCV) will be responsible for data collection from ‘targeted’ implementers. Each state has identified a data custodian to oversee this data collection and management. The study coordinating centre, Stillbirth CRE, will be responsible for the overarching evaluation and management of data provided to them from the health department (Fig. 3.). Investigators from the study coordinating centre will conduct surveys, focus groups, and one-to-one interviews with women, healthcare professionals, maternity service leads and implementation project leads.

**Fig. 3 Fig3:**
[figure not shown]
Data collection processes

#### Non-identifiable electronic extract of routinely collected perinatal data

Approval will be sought through the relevant state perinatal data collection custodians to access and analyse routinely collected population-based surveillance system data covering all births in NSW, VIC and QLD public and private hospitals over the study time period (covering 15 years’ pre-implementation to 2 years’ post-implementation). This non-identifiable electronic data will be extracted from each of the participating jurisdictions at yearly intervals throughout the duration of the project.

Monitoring and timely reporting of any unintended harm as a result of SBB implementation, such as increased unnecessary intervention and preterm birth, is essential [32]. Annual analysis of routine data extracts throughout both implementation and maintenance phases will allow for benchmarking of selected indicators. Reporting of comparisons for stillbirth rates and other important clinical outcomes will be for both ‘targeted’ and ‘non-targeted’ implementers. These comparisons will describe the effect of state-wide uptake of SBB components over time and consider any indirect impacts on antenatal care provision due to COVID-19 restrictions by jurisdiction.

Requested data items include: maternal demographics and medical history; previous pregnancy complications and birth outcomes; current pregnancy details; labour and birth outcomes; neonatal outcomes; and hospital demographics. Routinely collected hospital service utilisation data for each participating hospital will also be obtained as part of the SBB dataset. These data are routinely collected and reported to state health departments as part of minimum reporting requirements for activity-based funding.

#### Clinical audits and implementation process data

Jurisdictions may undertake and report a series of audits to assess process evaluation measures including missed cases of FGR, reporting of DFM and women birthing at term (measures such as risk assessment and management according to risk, smoking cessation support). Through these audit and feedback, benchmarking of key performance indicators will flag priority areas for practice change. ‘Targeted’ implementers will report on a standard set of process, impact and outcome measures for each of the five elements as part of their quality improvement strategies to implement. This data is important to understand the fidelity of the implementation strategies and sites will provide these implementation process data through the respective health departments (CED, CEC, SCV).

High quality clinical audit of all stillbirths to identify substandard care factors will be promoted through provision of the IMproving Perinatal Mortality Review and Outcomes Via Education (IMPROVE) program [33]. The data collection tool recommended by PSANZ [30] will be recommended for use across all participating maternity services to inform the standard clinical review of all stillbirths.

#### Surveys

Surveys will be undertaken at ‘targeted’ implementing sites. Surveys of women, healthcare professionals and maternity service leads are based on those used in the SBLCB evaluation [15] and will be administered electronically pre and post implementation (TP1). The self-administered surveys will be undertaken using an online survey software tool, Checkbox (Checkbox Survey Inc., Watertown, MA, USA) or REDCap [34]. Survey responses will be extracted from the on-line survey tool and imported into IBM SPSS statistics 24.0 for analysis.

##### Survey of women

This survey around care practices has been adapted from the UK SBLBC [15], in consultation with parents, clinicians and Aboriginal and Torres Strait Islander representatives on the investigator team, to include questions relevant to the SBB elements and to incorporate relevant International Consortium for Health Outcomes Measurement (ICHOM) data items for pregnancy and child birth [35]. Survey questions (n = 69) address demographic characteristics, pregnancy and birth outcomes, and experience of care received around the relevant elements of care. The survey questions are largely multiple choice with an option to provide comment. The survey will be administered to women following the birth (before hospital discharge or within 6 weeks of birth). Women who had a stillbirth or neonatal death prior to discharge from the hospital of birth will be excluded. Healthcare professionals will identify and approach all eligible women after the birth providing written materials along with a verbal explanation of the SBB study. Women will complete a self-administered on-line survey using a personal electronic device (i.e. phone, tablet, laptop) or electronic tablet provided by the study. By completing and submitting the survey, the women will be indicating consent to participate. Women will be reassured that nonparticipation or withdrawal from the study will not affect their routine care, relationships with professional staff or ongoing relationship with their health services provider.

##### Survey of healthcare professionals

Healthcare professionals providing antenatal care at ‘targeted’ implementing sites will be invited to complete an anonymous questionnaire to elicit attitudes, knowledge and practices around the SBB, pre- and post-implementation. The survey draws on the UK SBLBC [15] and consists of 50 questions and is constructed around 3 domains: demographics of clinicians (n = 10); clinicians current experience with care practices around SBB for each element (n = 38); clinicians views about service responsiveness (n = 2). For each element of the SBB there are questions around; the frequency of best practice for key recommendations; guideline availability; adequacy of training; satisfaction with resources; and clinician’s attitudes towards having conversations with women about these elements of care. There is consistency with our previous survey [18] of Australian maternity services in the rating scales for best practice frequency and questions relating to guidelines.

Eligible healthcare professionals will be identified and recruited by members of the respective site implementation teams. An e-mail invitation to participate in the survey will be circulated to all healthcare professionals providing antenatal care and will include a link to the on-line survey. The survey may also be distributed (on behalf of the Stillbirth CRE) by professional colleges including (but not limited to) the Australian College of Midwives, Women’s Healthcare Australasia and the Royal Australian and New Zealand College of Obstetricians and Gynaecologists. This would increase the reach of the survey to include healthcare professionals across ‘non-targeted’ implementers. By completing the survey consent to participate is implied. Participant information provided outlines that participation is voluntary, and that nonparticipation will not affect workplace relations.

##### Survey of maternity services leads

Based on that used in the UK SBLBC [15], this survey will be undertaken at ‘targeted implementer’ sites to examine the perceived level of implementation, and the impact on leadership, governance and workforce culture on implementation and change in key indicators and clinical outcomes post-implementation (TP1). This survey will be finalised during the implementation period drawing on the specific implementation approaches across each jurisdiction.

Maternity service leads and/or implementation leads will be invited to complete a self-administered on-line survey. The list of eligible leads and the contact for each will be identified by the state project teams. A brief description of the study together with an invitation to participate and a link to the online questionnaire will be provided in an email invitation.

#### Focus groups and semi-structured interviews

At ‘targeted’ implementer sites qualitative data will be collected to gain a more nuanced picture of women’s, healthcare professionals and implementation project leads experiences of the SBB by providing insights that may not easily be captured in quantitative data. These include issues related to acceptability of the various components of the SBB as well as important questions about possible differences in implementation, uptake and effects. Purposive sampling of interview participants will enable key dimensions of interest to the study and its outcomes to be explored in detail. Semi-structured interviews or focus groups will enable pre-determined questions to be explored while also inviting discussion of issues that are of importance to participants. All interviews will be conducted by a skilled qualitative interviewer, digitally recorded and transcribed in full for thematic analysis. Interviews will take place either in-person or by phone or videoconference. Women’s partners will also be invited to participate where possible.

For recruitment of women (and their partners) to focus groups/interviews, a member of the research team will liaise with clinical staff to identify those eligible who will then be approached directly by the site research team. Additionally, women and healthcare professionals who complete surveys are asked to provide their details (separately) if they consent to being contacted for follow up research related to this project. Women will be reimbursed for time spent participating in these activities and reimbursed for reasonable out-of-pocket expense such as child care and parking. Healthcare professionals will be approached directly by the site investigator and invited to participate. Implementation project leads will be approached by investigators from the study coordinating team. Evaluation through surveys and one-to-one interviews with ‘targeted’ implementer project team leads will further explore site recruitment strategies, commitment, and engagement to the SBB initiative and the influence of leadership, governance and culture on implementation strategies and approach.

#### Educational programs evaluation

Log of attendance and/or completion will be collected via the on-line registration platform for educational programs for both eLearning and face-to-face. Evaluation of participant knowledge and confidence around the five elements of the SBB will be undertaken using an in-built on-line survey administered immediately before and after completion of the eLearning module.

#### Economic evaluation

A modelled health economic evaluation will be undertaken. The intervention costs will be obtained from the routinely collected health service utilisation data. In addition, health service and societal costs of stillbirth will be captured using publicly available data sources or data from peer-reviewed publications for women who have a stillbirth and those who do not, developed as a part of the Stillbirth CRE [1]. In partnership with the Stillbirth CRE the economic evaluation is being conducted by [name] from Monash University. The detailed protocol developed for this component of the evaluation will be published separately and is beyond the scope of this paper.

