### Targeted implementation of the SBB through state-specific programs

State health departments of NSW, QLD and VIC will promote the SBB initiative across all maternity services in their jurisdictions, however, initial rollout involves targeted support to hospitals recruited to state-specific SBB implementation programs. Commencement dates, recruitment strategies and implementation approaches differ across jurisdictions but the intent for all is to progressively embed the SBB within existing care over a 12-24 month implementation period (post-launching). Each jurisdiction nominated a division (within their health department) to oversee the implementation process and data collection as follows: Safer Care Victoria (SCV, VIC Government), Clinical Excellence Commission (CEC, NSW Government) and Clinical Excellence Queensland (CEQ, QLD Government). In their capacity as state health care quality and safety improvement agencies, they are responsible for recruitment of ‘targeted’ implementers, implementation of the SBB in these sites and data collection for the purposes of the process and impact evaluations.

A key strategy used to optimise uptake of the SBB is having a dedicated implementation (quality improvement) project team for each jurisdiction, led by health service executive leadership teams. These teams will provide support through to the end of the project with the aim to see changes incorporated into business as usual. They will provide leadership, generate and sustain motivation for change, provide tools to support practice change through education, audit and feedback, and benchmarking and implementation support forums to facilitate sharing of experiences of the SBB by clinical champions from across ‘targeted’ implementers. In each state, at least three implementation learning support forums will be conducted during the implementation period, bringing together local implementation teams to discuss successes and challenges to enhance implementation. The Stillbirth CRE study co-ordination team will provide wide-ranging support across the jurisdictional implementation programs through attendance and participation at learning forums and representation on project teams and high-level committees. During both implementation and maintenance phases of this study, the Stillbirth CRE will report annual benchmarking of selected indicators and support national forums to share learnings.

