		Caesarean section; elective; emergency (caesarean section birth after labour)
		Admission to intensive care
		Unplanned returned to theatre

^a^Perinatal Society of Australia and New Zealand (PSANZ) classification [30], ^b^Australian and New Zealand Neonatal Network (ANZNN) criteria [31]

**Economic measures** will evaluate incremental cost-effectiveness of the SBB compared to standard care, total and incremental costs to the health system, and total and incremental costs to society. Measures include all inpatient and outpatient health service utilisation from first antenatal booking to six weeks postpartum including antenatal ultrasound scans and maternal and neonatal length of stay from routinely collected administrative data sources.

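### The only source named for intervention costs is routine service-utilisation data, which would not be expected to hold the cost of delivering the bundle

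*Protocol article*

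**What the plan says.** The Economic evaluation section announces a modelled evaluation and names one source for the cost of the intervention: "The intervention costs will be obtained from the routinely collected health service utilisation data". The sentence after it adds public and published sources, but only for the health-service and societal costs of stillbirth. The section then defers the detail: "The detailed protocol developed for this component of the evaluation will be published separately and is beyond the scope of this paper".

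The economic measures paragraph under Evaluation measures sets the scope as "incremental cost-effectiveness of the SBB compared to standard care, total and incremental costs to the health system, and total and incremental costs to society". It describes the data to be used: "Measures include all inpatient and outpatient health service utilisation from first antenatal booking to six weeks postpartum", with antenatal scans and maternal and neonatal length of stay given as examples. The section on the perinatal data extract says of the hospital utilisation data: "These data are routinely collected and reported to state health departments as part of minimum reporting requirements for activity-based funding".

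The intervention is described in two other places. The section on targeted implementation names as a key strategy "having a dedicated implementation (quality improvement) project team for each jurisdiction, led by health service executive leadership teams", with education, audit and feedback, benchmarking and at least three learning forums in each state. The Safer Baby Bundle section adds eLearning and face-to-face training for clinicians, materials for women and families, and a communications campaign.

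**The concern.** The article states a source for a quantity, and on its own description that source does not fit the quantity. Activity returns record what happens to patients: visits, scans, admissions and bed days. They can show whether the bundle changes the amount of care given. They would not be expected to show what it costs to run a team in a state health department, hold a forum, release staff for training or run a campaign.

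Economic evaluation is the fourth study aim, and the Discussion looks ahead to the remaining Australian jurisdictions taking up the bundle. A new jurisdiction would have to fund programme delivery, so that cost should not drop out. Leaving it out would move the ratio in one direction only, in favour of the bundle.

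**Working it through.** The article reports no cost, cost-effectiveness ratio or programme budget, so there is no figure to reproduce. The check has two parts.

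**1. Does the named source cover the intervention?** Each component is set against the data as the article describes them.

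| Component | Where described | Expected in inpatient and outpatient activity returns? |
|---|---|---|
| State project teams | Targeted implementation | No |
| Learning forums | Targeted implementation | No |
| Audit, feedback and benchmarking | Targeted implementation | No |
| Support from the study co-ordination team | Targeted implementation | No |
| eLearning and face-to-face training | The Safer Baby Bundle | No |
| Materials for women; awareness campaign | The Safer Baby Bundle | No |
| Scans and length of stay | Economic measures | Yes |

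The third column is an inference from the description of the data. The article does not itself say that programme costs are absent from them. No section shown names another source for the cost of the first six rows.

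**2. Direction and scale if the source is used alone.** Write the ratio as

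(change in care costs + programme cost C) / stillbirths averted.

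If C is left out and the bundle averts stillbirths, the ratio is too low by C / stillbirths averted.

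Inputs, from the Clinical outcomes part of Sample size and data analysis: 113,000 births a year at targeted sites, and a rate falling from 2.4 to 1.9 per 1000.

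Stillbirths averted a year = 113,000 x (2.4 - 1.9)/1000 = 113,000 x 0.0005 = 56.5.

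C is assumed over a range because the article gives no value:

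| Assumed C omitted, per year | C per birth (C / 113,000) | Ratio too low by (C / 56.5) |
|---|---|---|
| $0.5 million | $4.42 | about $8,850 |
| $1 million | $8.85 | about $17,700 |
| $5 million | $44.25 | about $88,500 |
| $10 million | $88.50 | about $177,000 |

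The shortfall scales inversely with the effect. At half the target effect, 28.25 stillbirths are averted a year, and $1 million omitted lowers the ratio by 1,000,000 / 28.25, or about $35,400.

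**The case against.** The strongest reply is that the article hands the costing to a separate economic protocol, and an itemised list of cost sources belongs there. That stands as far as it goes: nobody reading the article alone can say that the final analysis will leave programme costs out. It does not rescue the sentence, which states a source instead of leaving it open. If the separate protocol costs the programme from other records, the article's sentence is at odds with it and still needs correcting.

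A second reply is that the term intervention costs may mean the costs of care given under the bundle, for which utilisation data are the right source. That reading is possible, and some bundle activity is patient-level care. On that reading, however, the article names no source at all for delivery costs, although its stated scope is "total and incremental costs to the health system, and total and incremental costs to society". That scope would naturally include delivery costs, and it suggests that the investigators did not mean to exclude them.

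Third, other sources may exist. The list of economic measures is worded as open. A survey of maternity service leads at the end of implementation is to cover changes in resource use (Evaluation design). Training attendance is logged (Educational programs evaluation). Fig. 2, which links data tools to the economic evaluation, is not reproduced in the text available. These points leave room for another source, but no text shown ties the survey or the logs to the costing. The fuller description of the survey concerns the level of implementation, leadership, governance and culture, and it goes to leads at targeted sites, so it would not obviously capture state-level spending.

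A reader might infer that the cost-effectiveness ratio is already biased in favour of the bundle, or that a figure can be put on that bias. The documents support neither. The first depends on a protocol that is not shown, and the second on a programme cost that is not given.

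**Conclusion.** The point holds in conditional form. The article names a source for intervention costs that, as described, would not be expected to contain the cost of delivering the intervention. If the source is used alone, total and incremental costs are understated and the cost per stillbirth averted is too low.

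The direction follows from the arithmetic, provided that the bundle averts stillbirths and programme cost is above zero. The size cannot be determined. The figure of about $17,700 for each $1 million a year omitted rests on the full target effect at targeted sites, on an assumed programme cost, and on cost per stillbirth averted as the ratio, a denominator that the article does not specify.

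This is a badly fixed data source for a secondary aim. It is worth correcting and does not touch the primary outcome.

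**What to change.** Reword the sentence in the Economic evaluation section so that it separates two components. Routine utilisation data supply the costs of care from booking to six weeks postpartum. Programme delivery costs (project teams, forums, training, audit and feedback, resources, campaign) come from programme expenditure records and, for training, from the education attendance and completion logs. State that both enter the incremental cost. Then confirm that the separate economic protocol says the same, and align the two if it does not.

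The rewording is slight. The real cost is collating expenditure records. The article does not say in what form these exist, or whether staff time for audit and forums is recorded so that it can be costed. Such time is easier to record as it is spent than to reconstruct later. The other consequence is a less favourable ratio than utilisation data alone would give.

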### Sample size and data analysis

#### Clinical outcomes

Based on the most recent 3 year period prior to the SBB rollout, for which data are currently available (2016-2018), the late gestation stillbirth rate in Australia was 2.4 per 1000 births (unpublished data Stillbirth CRE). This decreased from 2.7 per 1000 births in 2013-2015 [6]. The SBB initiative aims to amplify and sustain a further rate reduction of at least 20% to target a rate of 1.9 per 1000 births by the end of 2023. Maintaining a downward pressure on rates is challenging given that as rates get lower further reductions may become increasingly more difficult to attain.

Based on 113,000 births per year across ‘targeted’ implementers, the study will be able to estimate a stillbirth rate of 1.9 to a precision of 1.7 to 2.1, with 95% confidence: 430 stillbirths out of 113,000 x 2 =1.9 per 1000 births. Put another way, the project will have 95% power (alpha=5%, two-sided) to show that an achieved stillbirth rate of 1.9 per 1000 births (the target for 2022-2023) is statistically significantly different from a stillbirth rate of 2.4 per 1000 births (pre-implementation for 2016-2018).

Secondary endpoints including obstetric intervention and other important maternal and newborn outcomes measurable using routine data will be analysed using analysis, similar to the pre-specified primary endpoint. Formal power calculations for the secondary endpoints have not been done due to statistical multiplicity. Point estimates for these secondary endpoints will be checked to confirm they are consistent with the result for the primary endpoint. Any outlying results will be investigated. Descriptive statistics will be used to summarise data such as demographic characteristics.

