## Background

Stillbirth is a tragic event for the woman, her partner, family and friends, as well as the healthcare professionals involved. Stillbirth imparts significant costs across the health system and society [1]. Every day in Australia six babies are stillborn, amounting to more than 2000 deaths a year [2]. For Aboriginal and Torres Strait Islander and some migrant and refugee communities (South Asian [3] and African [4]), stillbirth rates are often doubled [5].

In 2015, the stillbirth rate after 28 weeks’ gestation in Australia was 35% higher than countries with the lowest rates globally [6]. The average annual rate reduction at that time was 1.4%, ranking Australia 15th across high-income developed countries. Since then reductions in late gestation stillbirth rates have steadily improved [7, 8]; however, more can be done to reduce stillbirths in line with comparable countries [6]. A co-ordinated national approach to reducing practice variation and addressing areas of sub-optimal care provision is needed for further reductions in stillbirth. High quality clinical audits [9] suggest around 20 – 30% of late gestation stillbirths could be avoided with better care [10].

Working in partnership with parents, healthcare professionals, professional colleges, parent advocacy organisations, and government agencies, the Centre of Research Excellence in Stillbirth (Stillbirth CRE) identified key evidence-practice gaps in stillbirth prevention [11]. In early 2018, the Australian Senate convened a committee to inquire and report on the future of stillbirth research and education in Australia. The committee’s report [12] made a number of key recommendations encompassing improving the quality of antenatal care to address stillbirth in Australia. In response the government provided additional funding to the Stillbirth CRE to support national rollout of the Safer Baby Bundle (SBB), recognizing this key initiative to ensure that pregnant women are provided with high quality, evidence-based antenatal care that reduces the risk of stillbirth [13].

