## Methods

### Study aims and objectives

The overall purpose of this study is to determine the impact of implementing the SBB on Australian maternity services and perinatal outcomes. The primary aim is to (1) demonstrate the effectiveness of the SBB in reducing late gestation stillbirth rates (28 weeks’ gestation or more). The study also aims to: (2) understand the processes and contextual factors influencing implementation success; (3) determine the impact of the SBB on change in awareness, knowledge, behaviours and experiences around providing or receiving antenatal care for healthcare professionals and women respectively; (4) to undertake an economic evaluation of the SBB.

The study’s primary objective is to compare stillbirth rates at 28 weeks’ gestation or more across Australian maternity settings pre and post implementation of the SBB. Secondary objectives include:
Using routinely collected perinatal data to assess the endpoint effectiveness of the SBB for other important clinical outcomes, including any unintended consequences such as increased unnecessary intervention and preterm birthTo explore variations in the provision of antenatal care influencing disparities in stillbirth rates for Aboriginal and Torres Strait Islander, migrant and refugee, and rural and remote womenTo evaluate the coverage, acceptability, feasibility, fidelity, and sustainability of the SBB initiative and its implementation across settings and for different stakeholdersTo explore indirect process and contextual factors influencing antenatal care provision in relation to the SBB elements due to COVID-19 pandemic restrictions through interviews and surveys with project leadsTo explore the views and experiences of women and maternity healthcare professionals with antenatal care in relation to the five SBB elements utilising surveys, focus groups and interviewsTo estimate the cost-effectiveness of the SBB compared to standard care.

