### Evaluation design

A mixed-methods approach will be used to assess the processes, impacts and outcomes for the SBB initiative. Change in rates for the primary clinical outcome, stillbirth rate at 28 or more weeks, will compare the pre-implementation rate (including longer term trends over 15 years) with the rate in the 2 year post-implementation period (Time Point 2 (TP2)), using routinely collected perinatal data (see Fig. 1.) To allow for differences in commencement dates between jurisdictions and implementation disruptions due to COVID-19 restrictions, a 2.5 year implementation period is proposed. Key process and impact measures will be compared pre- (baseline) and post-implementation at evaluation TP1 including data from surveys of women and healthcare professionals, clinical audits and implementation process data. A survey of maternity service leads will be undertaken at TP1 (post-implementation) to assess changes in maternity services resource use, level of implementation and the influence of leadership, governance and workforce culture on implementation.

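### The stated 95% power is for a difference from a fixed 2016-2018 rate of 2.4 per 1000, not for an effect of the bundle beyond the decline already under way

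*Protocol article*

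**What the plan says.** Under Study aims and objectives, the first aim is to "demonstrate the effectiveness of the SBB in reducing late gestation stillbirth rates".

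The only quantified inference for that aim is in Clinical outcomes, under Sample size and data analysis. The claim made there is that "the project will have 95% power (alpha=5%, two-sided"). The comparator that this claim relies on is a single historical value: the post-implementation rate, taken as the 1.9 per 1000 set as the target, should prove "statistically significantly different from a stillbirth rate of 2.4 per 1000 births (pre-implementation for 2016-2018"). The post-implementation count is given as "430 stillbirths out of 113,000 x 2 =1.9 per 1000 births".

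On the background trend, the same section says of the 2.4 figure: "This decreased from 2.7 per 1000 births in 2013-2015". The Background section adds an older figure: "The average annual rate reduction at that time was 1.4" per cent, as of 2015, and says that reductions have improved since.

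Evaluation design describes the primary comparison differently from the power statement. It will "compare the pre-implementation rate (including longer term trends over 15 years) with the rate in the 2 year post-implementation period".

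**The concern.** The power calculation treats 2.4 as the rate that would have held in 2022-2023 without the bundle, yet the same section shows the rate falling before any state launched. If part or all of that fall would have continued anyway, a test against 2.4 measures the existing decline plus any bundle effect, and the 95% describes the chance of detecting the sum.

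Two things are at stake. First, a reader may take the 95% as assurance that the study can answer its effectiveness question, when the power for that question has not been given and may be far lower. Second, Clinical outcomes and Evaluation design describe different contrasts, so the stated power does not belong to the comparison that the article calls primary. Secondary endpoints are to be analysed in a similar way, so the ambiguity carries over to them.

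**Working it through.** **Inputs.** From Clinical outcomes: 2.7 per 1000 (2013-2015), 2.4 (2016-2018), target 1.9 (2022-2023), 113,000 births a year, two-sided alpha 5%. From Background: a 1.4% annual reduction as of 2015. The size of the pre-period is not stated; 226,000 births per period is an assumption.

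**1. The stated power.** Two-proportion normal test, power = Φ[(p1 − p2 − 1.96·SE)/SE], with SE ≈ √[2·p̄(1 − p̄)/n].
- p̄ = (0.0024 + 0.0019)/2 = 0.00215; SE = √(2 × 0.00215 × 0.99785/226,000) = 0.0001378.
- (0.0005 − 1.96 × 0.0001378)/0.0001378 = 1.67, so power = 95.2%.

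This reproduces the stated 95%. A three-year baseline of 339,000 births gives 97.8%. So the figure is arithmetically sound for a fixed 2.4.

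**2. The rate expected in 2022-2023 with no bundle effect.** Period midpoints are 2014.5, 2017.5 and 2023.0, so the projection runs 5.5 years past the 2016-2018 midpoint.
- Recent trend: annual decline = 1 − (2.4/2.7)^(1/3) = 3.85%; projection = 2.4 × (2.4/2.7)^(5.5/3) = 1.93. A straight line (0.1 per year) gives 2.4 − 0.55 = 1.85.
- Rounding: 2.75 falling to 2.35 projects to 1.76; 2.65 falling to 2.45 projects to 2.12.
- Older trend: 2.4 × 0.986^5.5 = 2.22.

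**3. Chance of a significant difference from the 2016-2018 rate with no bundle effect** (same test, 226,000 births per period; nominal 5%).

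| Assumed decline | Projected rate | Chance of significance |
|---|---|---|
| 3.85% a year | 1.93 | 92% (96% with a three-year baseline) |
| Linear, 0.1 a year | 1.85 | 98% |
| Rounding extremes, 2.35 to 1.76 and 2.45 to 2.12 | 1.76 and 2.12 | 99% and 64% |
| 1.4% a year | 2.22 | 24% (28% with a three-year baseline) |

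**4. Power to show that 1.9 lies below trend.** Log-linear Poisson model with intercept, yearly slope and a post-period step. Pre-years are taken as 2004-2018, post-years as 2022-2023, with 113,000 births a year throughout. Power comes from the Fisher information for the log rate ratio.
- Recent trend continues: RR = 1.9/1.934 = 0.982; |log RR| = 0.0177; SE = 0.064; power about 6%.
- 1.4% a year: RR = 1.9/2.221 = 0.855; |log RR| = 0.156; SE = 0.065; power about 67%.
- True 20% fall below trend: |log 0.8| = 0.223; SE 0.066 to 0.068; power about 91% to 92%.
- True 10% fall below trend: power about 36% to 38%.

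At the lowest projection, 1.76, a rate of 1.9 would lie above the trend.

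**The case against.** The strongest reply is that the power sentence is not the primary test. It restates a precision statement and names no model. Evaluation design puts 15-year trends into the primary comparison, 15 years of pre-implementation data are requested, and the way the trend enters the model can properly be left to an analysis plan. That stands. A reader might infer that the plan is committed to a flat before-and-after test and so cannot show effectiveness at all. The article does not support that reading. It also plans comparisons of targeted with non-targeted sites, by state, and by level of implementation, and these bear on secular trend. Their help is limited: the targeted comparison carries no stated power, targeted sites joined by expressing interest, and Study setting says that all hospitals will be exposed to the initiative.

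A second reply is that 1.93 is fragile. It extrapolates two rounded rates for Australia from different sources, while the primary outcome is restricted to singletons without lethal anomalies and the power applies to targeted sites. The article warns that further falls may become harder, and raises concern that rates may increase during the pandemic. All of this stands, and it is why a range is needed. It does not restore the 95%: even the slower quoted decline gives about five times the nominal error rate.

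A reader might also infer that the hoped-for 150 lives a year would be computed from this test. The article presents that figure as a hypothesis about national scale-up, not as a result of the comparison.

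**Conclusion.** The concern holds in this form: the 95% is correct for 1.9 against a fixed 2.4, but it is neither power for a bundle effect nor power for the trend-inclusive comparison in Evaluation design. A significant difference from 2.4 would not, on its own, separate the bundle from the existing decline. With no bundle effect it would occur in about 24% (1.4% a year) to 92% (recent decline continued) of cases, and power to show 1.9 below trend runs correspondingly from about 67% down to 6%.

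These figures assume 226,000 births per period for the flat test and 15 pre-years at 113,000 births a year for the trend model, no variation beyond binomial or Poisson, and national rates standing in for the endpoint in targeted sites. A slowing decline or a pandemic rise would move the projected rate up. The design remains useful: a true 20% fall below trend would be detected with about 91% to 92% power under the same model.

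**What to change.** - Define the primary effect as the departure of the 2022-2023 rate from the rate predicted by the pre-launch trend, and say so in both Evaluation design and Clinical outcomes. A segmented Poisson or negative-binomial regression with births as offset, fitted to the 15 pre-implementation years, is one suitable model.
- Replace the 95% with the power for that contrast over a stated range of projected rates, about 1.76 to 2.22 per 1000, and state the size of the pre-period.
- Express the planned reduction relative to the projected rate, and describe 1.9 against 2.4 as attainment of the target, not as evidence of effectiveness.
- Acknowledge that a departure from trend would still absorb any pandemic effect on stillbirth rates.

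The cost is revised wording and a less favourable power figure. No new data are needed, since the 15-year extract is already requested.
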